### Interventions

#### Treatment Condition (computer based co-morbidity treatment)

Individuals in this condition will complete the SHADE program [25]. Participants will attend two × 1-hour sessions each week, completing the program in five-weeks (approximately 10 h of engagement with SHADE in total). These sessions will be conducted on computers located at the Recovery Service Centre. Research assistants will provide technical support whilst participants are completing the program (e.g. helping the person to become familiar with using the program), but will not provide any clinical support. The SHADE program is a clinical intervention that incorporates aspects of motivational interviewing and CBT. The program content is delivered in an integrated fashion and is designed to encourage a reduction in depression and alcohol and/or substance use. The program contains interactive components, including video demonstrations, voiceovers and in-session exercises. The video components are viewed and model the cognitive and behavioural skills relevant to the therapy (e.g. activity scheduling, self-monitoring of thoughts, challenging faulty cognitions, identifying and evaluating cognitive schema, drink/drug refusal and problem solving).

#### Active Control Condition (computer delivered typing tutor program)

A limitation with previous computer based intervention studies is the lack of an active control condition [22]. To address this concern we have included a computer delivered typing tutor to control for the amount of screen time participants in the treatment condition experience. Participants in the active control condition will complete a commercially available typing tutor program [30]. This program has previously been used as an active control in studies examining computer delivered cognitive remediation for participants attending residential substance abuse services [31]. Participants will attend two × 1-hour sessions each week, completing the computer delivered typing program in 5 weeks (approximately 10 h in total). This is comparable to the Treatment condition. These sessions will be conducted on computers located onsite and, as with the Treatment condition, research staff will be available to support participants with the technical aspects associated with using the computer program.

#### Treatment as usual (TAU)

Participants in both the Treatment and Control conditions will be completing The Salvation Army Recovery Service Centre program (i.e. TAU). The program utilises a 12-Step approach and is primarily based on the disease model of addiction. Participants attend individual case management, group therapy sessions and regular chapel services. Groups provided during the program cover a diverse and eclectic range of areas including social skills training, relapse prevention planning, family systems work and anger management. However, participants do not have access to cognitive behavioural therapy. The program does not specifically address co-occurring mental illness, although participants may be under the care of an external medical practitioner and be taking psychiatric medication.

#### Outcome measures

Baseline assessments will be conducted prior to notification of randomization status. This will include administering the Structured Clinical Interview of the DSM IV [SCID; [32]] to identify 12-month and lifetime history of alcohol or other substance abuse and dependence disorders. Additionally, 12-month and lifetime history of depressive disorders will also be assessed using the SCID. Outcome measures will be collected at baseline, weekly during the 5 weeks of the treatment program and then at 3-, 6-, 9-, and 12-month follow-up (see Table 1 for schedule). Independent assessors, who will remain blind to intervention allocation, will conduct follow-up telephone assessments to collect this data. Each participant will be offered $20 AUD for completion of the baseline assessment and each subsequent follow-up assessment, as reimbursement for the time associated with completing the measures. Participants will receive $10 AUD for each assessment completed during the treatment program. For assessments completed while a participant is a resident at the Recovery Service Centre, he or she will be remunerated in cash. For telephone assessments completed once the participant leaves the program, gift certificates will be mailed out.

**Table 1 T1:** Assessment instruments proposed for the current study

Domain assessment and instrument used	Baseline	Weeks	Week	Months
		
		1 to 4	5	3, 6, 9,12
**Diagnostic Assessment**				

Structured Clinical Interview for DSM Disorders: depression and substance abuse sections only	✓			

**Alcohol and substance abuse measures**				

Addiction Severity Index: Alcohol and Drug composite scores	✓		✓	✓

Alcohol Use Disorders Identification Test	✓			

Drug Abuse Screening Test	✓			

Opiate Treatment Index	✓		✓	✓

Drug Taking Confidence Questionnaire	✓	✓	✓	✓

PENN Alcohol Craving Scale	✓	✓	✓	✓

Drug Risk Response Test	✓		✓	

Fagerstrom Test for Nicotine Dependence	✓	✓	✓	✓

**Mental health measures**				

Addiction Severity Index: Mental Health composite score	✓		✓	✓

Depression, Anxiety and Stress Scale	✓	✓	✓	✓

Beck Fast Screen	✓	✓	✓	✓

Dysfunctional Attitudes Scale	✓	✓	✓	✓

Ways of Responding	✓		✓	

**Other**				

Background and demographic information	✓			

Addiction Severity Index: Employment Status composite score	✓			✓

Client Satisfaction Survey			✓	

Computer Attitudes Scale	✓	✓	✓	

#### Primary outcome measures

The two primary outcome variables will be: a) level of substance use; and b) level of depression. The level of substance use will be measured using the composite scores for alcohol use and drug use from the Addiction Severity Index - 5^th ^Edition [ASI; [33]]. The ASI is a semi-structured clinical interview that has been used widely in addiction research [34]. The Opiate Treatment Index [OTI; [35]] will be used as an alternate measure of alcohol and substance use in the last month. The OTI yields a score reflecting the mean number of substance use occasions per day for each drug class assessed for the month prior to assessment. The Timeline Follow-Back Method [TLFB; [36]] will be used to improve participants' recall of their alcohol and substance use on the ASI and OTI. The TLFB method yields high test-retest reliability and has been used successfully in both face-to-face and telephone delivered assessment procedures [37,38]. The Beck Depression Fast Screen [BDFS; [39]] and the depression subscale of the Depression, Anxiety and Stress Scale [DASS-21; [40]] will be used to examine changes in depression levels during the course of the study.

#### Secondary outcome measures

A requirement of treatment in the residential facility is that participants do not use any alcohol or non-prescribed substances of abuse. Therefore, to be able to examine alcohol and substance use outcomes whilst a person is a resident of the program, secondary outcome measures will be included that examine cravings for the person's primary substance of abuse [PENN Alcohol Cravings Survey; [41]] and self-efficacy in terms of resisting the urge to drink alcohol or take drugs in specific high relapse risk situations [Drug Taking Confidence Questionnaire; [42]]. Additionally, the Dysfunctional Attitudes Scale [43] will be used to examine changes in the existence and intensity of dysfunctional attitudes commonly associated with depression. The ASI composite score for employment status will also be used to examine employment outcomes.

To examine the potential mechanisms of change associated with the SHADE program, two measures of coping skill acquisition will be included. The Drug Risk Response Test [DRRT; [44,45]] measures coping skills to manage circumstances in which there is a high risk for using alcohol or other drugs. It has been used in a number of studies exploring coping skill acquisition amongst individuals receiving treatment for substance use disorders [45-47]. The Ways of Responding Questionnaire [WOR; [48]] is a measure that examines coping skills in response to situations that increase the risk of depressed mood. Both the DRRT and the WOR involve the participant providing responses to hypothetical scenarios, with their responses providing an indication of both their adaptive and maladaptive coping skills. Research assistants blind to the participants treatment condition will rate both the WOR and the DRRT.

### Data-analysis

#### Power analysis

Data from the SHADE study [25] indicate that the computerized intervention is associated with a 1.53 effect size change for depression and 0.86 for alcohol between baseline and 12-month follow-up assessments. These effects sizes were entered into G-Power 3.1 [49] in order to estimate the sample sizes required to detect similar differences between the treatment and active control conditions in the current study. Power was set at 80% and conservative 2-tailed tests were assumed even though a directional hypothesis is proposed. The sample size needed to detect a similar effect size between groups on depression is 8 per group for depression (total N = 16) and 23 per group for alcohol (total N = 46). Given the SHADE studies compared the computerized intervention to a control condition consisting of only received a brief intervention and the proposed study is comparing SHADE + TAU to an active control condition + TAU, we anticipate smaller effect sizes. When a more conservative medium effect size of .50 is used, power is set to 80% and a 2-tailed test is used, a sample size of 64 per group is needed (total N = 128). A conservative drop out rate is 35% of participants at follow-up. As such, we will recruit a minimum of 200 participants to the study. This will ensure that we will have sufficient power to conduct the analysis.

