Cognitive Behavioural Therapy (CBT) is an approach that lends its self very successfully to being delivered in an integrated fashion. There is strong support for its effectiveness in the treatment of alcohol and substance abuse disorders [6], as well as across a wide range of psychiatric conditions [7]. Whilst CBT has demonstrated comparative effectiveness to other therapeutic approaches [8], it tends to have more durable long-term effects when compared to other treatment conditions [9]. For example, in a randomized trial comparing integrated CBT with a12-Step facilitation therapy for people diagnosed with substance dependence and depression, both interventions produced similar reductions in substance use and depression at the end of treatment [10]. However, participants in the integrated CBT condition continued to demonstrate improvements in their depression at 6-months follow-up, while depression for participants in the 12-Step condition deteriorated. More stable reductions in substance use were also demonstrated for people in the integrated CBT condition at follow-up.

Whilst there is increasing empirical support for integrated treatment approaches, the majority of substance abuse services do not address co-occurring mental illness in a systematic way. For example, a review of residential substance abuse services across three Australian states indicated that 88% of services were not equipped to provide integrated mental health treatment [11]. This appears to be largely the result of organisations employing people with limited or no mental health qualifications and failing to prioritise co-morbidity treatment [12]. Moreover, high staff turnover rates in the substance abuse field [13,14] makes attempts to train staff in new therapeutic approaches, such as integrated CBT, problematic and difficult to sustain in the longer term.

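### Change from baseline to 12 months is used as if it were a difference between arms, so 8 and 23 per group do not size this comparison and cannot make 0.50 conservative

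*Protocol article*

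**What the plan says.** All the sizing is in the protocol article, Data-analysis, Power analysis. From an earlier trial of the same program, it says that the computerised intervention "is associated with a 1.53 effect size change for depression and 0.86 for alcohol between baseline and 12-month follow-up assessments". These values went into G-Power "in order to estimate the sample sizes required to detect similar differences between the treatment and active control conditions in the current study". On power and sidedness: "Power was set at 80% and conservative 2-tailed tests were assumed even though a directional hypothesis is proposed". No alpha is given there. The sample size obtained "is 8 per group for depression (total N = 16) and 23 per group for alcohol (total N = 46").

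The section then notes that the earlier comparator was a brief intervention, whereas "the proposed study is comparing SHADE + TAU to an active control condition + TAU, we anticipate smaller effect sizes". The design calculation follows: "When a more conservative medium effect size of .50 is used", the requirement is 64 per group (128 in total). With 35% dropout, at least 200 are to be recruited.

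Two other sections bear on this. Treatment as usual (TAU) says that both arms complete the residential program. Analysis plan sets the significance threshold at p < 0.01 and plans mixed models.

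**The concern.** The inputs are described as change over time, but they are used as the distance between two arms. Change from baseline in a treated group contains whatever would have happened without the program: effects of other care, natural recovery, regression to the mean. A control arm shows those too, and they cancel in the between-group contrast. Here the control arm receives case management, group therapy and a residential stay, so assuming that it does not change is hard to defend.

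The reason given for expecting smaller effects is only that the comparator differs. The section does not recognise that the inputs are not between-group quantities in the first place. It offers no other support for 0.50 than the label medium and its position below 1.53 and 0.86: no between-group estimate, no control-arm change and no minimal important difference. If those two values are not on the right footing, a reader cannot tell whether 0.50 is cautious or hopeful, yet the section concludes that power is sufficient.

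**Working it through.** **Inputs.** From Power analysis: 1.53, 0.86 and 0.50; 80% power; two-tailed; 35% dropout; at least 200 recruited. From Analysis plan: threshold 0.01. Inferred: two-sided alpha 0.05 behind the sizing, because only this reproduces the stated figures.

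**1. Reproduce the plan's figures.** For a two-sample t-test with n per group, power = P(|T| > t_crit), where T is noncentral t with 2n − 2 degrees of freedom and noncentrality d·√(n/2). Solving for 80% power at two-sided 0.05:

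- d = 1.53: n = 7.79, so 8 per group
- d = 0.86: n = 22.23, so 23 per group
- d = 0.50: n = 63.77, so 64 per group

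All three match. The alternatives do not: one-sided 0.05 gives 7, 18 and 51; two-sided 0.01 gives 12, 34 and 96. A paired test, which would suit a change score, needs 6 and 13 participants *in total* for 1.53 and 0.86. So the change values were treated as between-group d.

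**2. Where the target comes from.** 128 / (1 − 0.35) = 196.9, so 197, rounded up to 200. Conversely 200 × 0.65 = 130 completers, or 65 per arm. The figures 8 and 23 do not enter.

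**3. What the change values imply between groups.** With c the control-arm change on the same SD scale, d_between = d_change − c. The document gives no c, so the values below are assumptions chosen to show the range (alpha 0.05, 80% power for n; power columns at 65 per arm).

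| Outcome | Assumed c | d_between | n per group | Power at 0.05 | Power at 0.01 |
|---|---|---|---|---|---|
| Depression | 0 | 1.53 | 8 | >99% | >99% |
| Depression | 0.50 | 1.03 | 16 | >99% | >99% |
| Depression | 1.00 | 0.53 | 57 | 85% | 66% |
| Depression | 1.25 | 0.28 | 202 | 35% | 16% |
| Alcohol | 0 | 0.86 | 23 | >99% | 99% |
| Alcohol | 0.25 | 0.61 | 44 | 93% | 80% |
| Alcohol | 0.36 | 0.50 | 64 | 81% | 59% |
| Alcohol | 0.50 | 0.36 | 123 | 53% | 29% |

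The stated 8 and 23 are the rows with c = 0. The value 0.50 ceases to be conservative when c exceeds 0.86 − 0.50 = 0.36 (alcohol) or 1.53 − 0.50 = 1.03 (depression).

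**4. The SD scale.** Step 3 takes the change to be standardised by an ordinary between-person SD. If it was standardised by the SD of the change scores, then d = d_z·√(2(1 − r)), with r the correlation between baseline and follow-up. For r = 0.3, 0.5 and 0.7 (assumed), 1.53 becomes 1.81, 1.53 and 1.19, and 0.86 becomes 1.02, 0.86 and 0.67. At r = 0.7 the break-even control changes fall to 1.19 − 0.50 = 0.69 and 0.67 − 0.50 = 0.17; at r = 0.3 they rise to 1.31 and 0.52.

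**5. What 65 completers per arm can detect** in a simple two-sample comparison at 80% power: d = 0.495 (about 0.50) at 0.05 and d = 0.607 (about 0.61) at 0.01. Power for d = 0.50 is 81% at 0.05 and 59% at 0.01.

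**The case against.** The strongest reply is that the criticised figures carry no weight. The section itself sets 8 and 23 aside and sizes the trial on 0.50, with a correct allowance for dropout. That stands: the recruitment target is untouched, and every number reproduces. What does not follow is that the figures are harmless, because they are the only yardstick against which 0.50 is called conservative.

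A second reply is that the cited values may in fact be differences in change between arms. The source is not at hand, so this cannot be excluded. But the text speaks of change from baseline to 12 months, and if something else was meant the wording needs correcting anyway.

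Third, the planned analysis is a mixed model on repeated measures that keeps participants with partial data. It may have more power than a t-test on completers. So the figures in step 5 are a benchmark on the basis that the plan itself used, not the power of the planned model.

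Three stronger readings are tempting and should be resisted:

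- A reader might infer that 0.50 is too large and the trial underpowered. The documents give no control-arm change, and for depression controls would have to improve by more than 1.03 SD before 0.50 exceeded the implied difference.
- A reader might cite the Background, where in a trial of integrated CBT against 12-step facilitation "both interventions produced similar reductions in substance use and depression at the end of treatment". The same paragraph goes on to report that CBT did better at 6 months, and that trial compared alternatives, not an add-on to 12-step care.
- A reader might infer that the plan claims a margin of 16 or 46 needed against 200 recruited. It does not: the stated requirement is 128 completers, and 197 against 200 leaves almost no margin.

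**Conclusion.** The point holds in a limited form. As written, 8 and 23 per group are correct arithmetic on the wrong kind of effect size, and they are valid for the between-group question only if the control arm does not change over 12 months. They therefore cannot justify describing 0.50 as more conservative. The documents show that 0.50 lacks support from these figures; they do not show that it is wrong.

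This rests on reading 1.53 and 0.86 as the text describes them. The break-even values of 0.36 SD (alcohol) and 1.03 SD (depression) further assume a common SD scale. The mismatch between the implied alpha of 0.05 and the p < 0.01 threshold is a separate matter. It enters here only because a statement of detectable effect has to be made at the threshold that will be used.

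**What to change.** In Power analysis:

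1. Delete the 8 and 23 per group figures. If the team has the earlier trial's 12-month difference between SHADE and its control, quote that instead, labelled as between-group.
2. Remove the phrase more conservative as applied to 0.50, and present 0.50 as the chosen target difference, with a reason for the choice. The same adjective applied to two-tailed testing and to dropout is not affected by this point.
3. State what about 65 completers per arm can detect with 80% power in a simple two-sample comparison: d = 0.50 at 0.05, and d = 0.61 at the p < 0.01 threshold in Analysis plan, where power for 0.50 is about 59%.

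The cost is rewording one paragraph. Enrolment and procedures do not change. The drawback is that the stated power looks less favourable and the closing assurance of sufficient power has to be qualified.

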#### Analysis plan

Data coding and analysis will be carried out by the authors using available software packages. Variables hypothesised to change over time according to treatment allocation will be examined predominantly using generalized linear mixed models. These techniques facilitate management of missing data without imputing values or excluding participants. Primary outcome measures will typically be analysed in two ways: a) intention to treat; and b) analyses performed within the sub-sample of participants who completed the majority of treatment sessions. In addition, comparisons on selected demographic and clinical characteristics will be made between this sub-sample and those who dropped out of treatment, to help detect any biases in outcome measures. Other potential confounders will also be examined (e.g. involvement in additional mental health treatments) and their potential effects will be modelled in the major analyses (e.g., controlling and not controlling for these variables). As a partial control for the number of statistical tests to be conducted, the threshold for significance will be set at p < 0.01.

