A significant challenge for this project will be participant dropout due to participants leaving the residential treatment facility prior to completing the intervention. Dropout rates from substance abuse treatments are extremely high. Fifty-seven percent of participants prematurely leave within the first 3-months of treatment [50]. Similar percentages have also been reported in the broader alcohol and other substance abuse treatment literature [see [51] for review]. To help address this concern, participants will complete the SHADE or computer delivered typing interventions twice a week (i.e. over a 5-week period). This represents a shift from the protocol used by Kay-Lambkin et al. [25], where SHADE was delivered weekly for 10-weeks.

A further challenge for the study will be retaining participants at follow-up. People with alcohol and other substance abuse disorders are traditionally very difficult to follow-up. This is further complicated with residential facilities, as participants often move outside of their local area to attend treatment. Attempts to improve follow-up rates in the current study will include using telephone follow-up, obtaining contact details of significant others to help with locating participants, reinforcing to participants the importance of conducting follow-up and financially compensating participants for the time required to complete the assessments (AUD$20).

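### The completer analysis of the primary outcomes is not protected by randomisation and is not ranked below ITT; it should be exploratory, with a complier-average estimate as the main attendance-related analysis

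*Protocol article*

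**What the plan says.** The Analysis plan section states: "Primary outcome measures will typically be analysed in two ways: a) intention to treat". The second way is "analyses performed within the sub-sample of participants who completed the majority of treatment sessions". The section does not say which analysis carries the conclusion, does not call the second supportive, and does not say whether the restriction applies in both arms. As a check for bias it adds that "comparisons on selected demographic and clinical characteristics will be made between this sub-sample and those who dropped out of treatment".

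The Interventions section gives both arms two one-hour sessions a week for five weeks, ten in all. Content differs: motivational and CBT material under SHADE, a commercial typing tutor under control.

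Strengths and limitations expects early departure to be a major difficulty, naming "participant dropout due to participants leaving the residential treatment facility prior to completing the intervention" and citing this rate: "Fifty-seven percent of participants prematurely leave within the first 3-months of treatment". The power analysis plans for an effect of 0.50 SD and at least 200 participants. The significance threshold is p < 0.01.

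**The concern.** Whether someone completes most sessions is known only after allocation and may depend on it. Those who stay with ten hours of unsupported CBT content need not resemble those who stay with ten hours of typing practice. If they differ in prognosis, the completer contrast mixes that difference with any treatment effect, in either direction.

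The planned check looks elsewhere. Comparing completers with dropouts describes who left, whereas the contrast at risk is SHADE completers against control completers. The check might hint at differential selection on measured traits if done separately by arm, but it corrects nothing.

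At stake is the reading of the trial if the two analyses disagree. The article presents an effectiveness study in a real-world setting, which ITT answers. Yet its Discussion words the mental health expectation as SHADE completers against everyone allocated to control.

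**Working it through.** **Inputs from the article.** Ten sessions at two a week; 57% leaving within 3 months; planned effect 0.50 SD; 200 recruited, taken here as 100 per arm; threshold p < 0.01. The plan gives no figure for completion or for bias, so there is none to reproduce.

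**Assumptions.** Three months is 13 weeks; leaving occurs at a constant rate; the clock starts at session 1. The last is doubtful for residents already 4 weeks or more into the program at entry. The completion gaps between arms and the trait-outcome correlations are hypothetical.

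**Step 1: plausible completion.** A majority of ten sessions is at least six, reached at the end of week 3.
- Still resident at week 3: 0.43^(3/13) = 0.823
- Still resident at week 5: 0.43^(5/13) = 0.723

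These set only a rough scale for completion. They say nothing about a difference between arms.

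**Step 2: bias with no true effect.** Let people complete when a standard normal trait exceeds a threshold, and let r be its correlation with outcome. With completion proportion p, the mean trait among completers is m(p) = φ(Φ⁻¹(p))/p:
- m(0.82) = 0.320
- m(0.72) = 0.468
- m(0.62) = 0.614

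Bias = r × [m(p in one arm) − m(p in the other)].

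| Completion by arm | Difference in m | r = 0.3 | r = 0.7 |
|---|---|---|---|
| Equal, same selection | 0 | 0 | 0 |
| 72% v 82% | 0.147 | 0.04 SD | 0.10 SD |
| 62% v 82% | 0.294 | 0.09 SD | 0.21 SD |

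The largest value is 0.206/0.50 = 41% of the planned effect. It combines the largest gap with the largest correlation.

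**Step 3: weaker and different selection.** If prognosis correlates 0.5 with completion and 0.5 with outcome, the multiplier is 0.25, and the two gaps give 0.25 × 0.147 = 0.04 and 0.25 × 0.294 = 0.07 SD. Equal completion rates do not guarantee safety. With 60% completing in both arms but selection related to prognosis only under SHADE, the bias is 0.25 × m(0.60) = 0.25 × 0.644 = 0.16 SD. The same value applies if SHADE completers are compared with all controls.

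**Step 4: false-positive rate at p < 0.01, before loss to follow-up.**
- 72 and 82 completers: SE = √(1/72 + 1/82) = 0.161. Biases of 0.044 to 0.103 raise the two-sided error from 1% to about 1.3% to 2.7%.
- 62 and 82 completers: SE = √(1/62 + 1/82) = 0.168. Biases of 0.088 to 0.206 give about 2.1% to 8.8%.

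**Step 5: the complier-average estimate.** This is the ITT difference divided by the proportion p who receive SHADE. The article describes no route by which controls receive SHADE, so only the SHADE arm can depart from its allocation. With no true effect the estimate is zero however completion is selected.

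If receipt means the majority of sessions, the method assumes that attending fewer has no effect. Suppose completers gain 0.50 and non-completers gain 0.25. The estimate is then 0.50 + 0.25 × (1 − p)/p:

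| p | Estimate (true completer effect 0.50) |
|---|---|
| 82% | 0.55 |
| 72% | 0.60 |
| 60% | 0.67 |
| 50% | 0.75 |

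Its standard error is about 1/p times that of ITT. At 72% that is 1.39 × √(2/100) = 0.196, against 0.161 for the completer contrast in Step 4.

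**The case against.** A reader might infer that the completer analysis is biased. The article does not show that. Bias requires selection that differs between arms, and the cause of non-completion it names is leaving the residence, which both arms share. Sessions are matched in number, length and site, and controls are given their own reason to attend. This stands: the supportable statement is that the contrast is unprotected, with bias of unknown size and direction.

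The size of the bias rests on invented gaps and correlations, and at the strict 0.01 threshold a 10-point gap raises the error only modestly. This also stands, and the figures should be read as a range of scenarios.

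A reader might also infer that the completer result is meant to share or take over the primary role. The text does not support that. ITT is listed first, the main models follow treatment allocation, and a full protocol or analysis plan may rank the analyses. What remains is that the published text commits the primary outcomes to both analyses and attaches no caveat to the second beyond a check that cannot correct it.

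Finally, a complier-average estimate might look like a clean replacement. With a six-session cut-off it is not. Under partial benefit at 72% to 82% completion it overshoots by 0.05 to 0.10 SD, about as much as the bias a 10-point gap would cause. This changes how receipt should be defined, but the estimate still stays at zero under the null, which the completer contrast need not do.

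**Conclusion.** The point holds as a limited one about the second analysis. The completer contrast is defined after randomisation by attendance at different programs, stands unranked beside ITT, and has a safeguard that cannot correct differential selection. Its bias may be nil. Under assumed completion gaps of 10 to 20 points and trait-outcome correlations of 0.3 to 0.7 it is about 0.04 to 0.21 SD. The true figure cannot be derived from the article, which has no completion rates by arm. The ITT analysis is unaffected. The change is cheap and worth making.

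**What to change.** 1. State that ITT is the sole basis for the primary conclusions.
2. Label the completer analysis exploratory, and say whether the restriction applies in both arms.
3. Report sessions attended by arm, and compare SHADE completers with control completers at baseline.
4. Make a complier-average estimate, with randomisation as the instrument and the same covariates, the main attendance-related analysis. Define receipt as any SHADE attendance or as the number of sessions attended. If the majority cut-off is kept, state that it assumes no effect of fewer sessions and give a sensitivity range for partial benefit.

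**Cost.** A little analysis work and wording; the only data needed are attendance records. The complier-average interval is wider than that of the completer contrast, and the estimate adds no power over ITT. It does not correct selection from the 35% loss at follow-up that the power analysis allows for.
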